### Study population

#### Inclusion criteria

To be eligible to participate in this study, a subject must meet all of the following criteria:Carcinoma located in the colon and rectosigmoid defined as a tumour located 15 cm above the anal verge by coloscopy or above the sacral promontory as seen preoperatively;Stage I, II, or III carcinoma;Surgical treatment with curative intent;Qualified for routine follow-up attendance by surgeon or oncologist according to the national guideline;Patients who have temporary stoma and who received adjuvant chemotherapy are also eligible.

#### Exclusion criteria

A potential subject who meets any of the following criteria will be excluded from participation in this study:Stage IV colorectal tumours;Hereditary colorectal cancer (e.g., Lynch and familial adenomatous polyposis);Colorectal cancer in patients with inflammatory bowel disease;Rectal cancer;(Sub)total colectomy or proctocolectomy;History of second primary cancer (except basal cell carcinoma of the skin) within the last 15 years;Participation in other (clinical) research, which will affect the outcome measurements of this trial;Permanent open wounds after surgery or other conditions in which specialised care is needed;Any other condition that warrants increased intensity of surveillance with respect to colon cancer follow-up;Not able to speak and read Dutch or English.

#### Inclusion procedure

Patients are asked for their informed consent postoperatively after the results of the pathological examination of the resection specimen with its consequences have been discussed with the patient. Patients will be recruited by treating physicians at the different hospitals. The treating physician will inform patients, and written informed consent is obtained by the research team. Participants will be given as much time as they desire to consider their decision.

### Intervention

#### Intervention 1 (GP-led follow-up and aftercare)

Guidelines for follow-up will be according to the national guideline for colon carcinoma [2]. The follow-up guideline is similar in both arms. GPs allocated to the intervention arm are given written instructions on what to do if recurrence is suspected and this mainly includes prompt re-referral. The follow-up guidelines have been summarized in a survival care plan especially to support the participating GPs. This survival care plan also contains information on possible physical and psychosocial problems patients might have and subsequent interventions. In case of questions regarding the information in the letter or in the survival care plan, relevant contact information will be supplied. The survival care plan will also be available at the study website (see http://www.icarestudie.nl/). Also, both surgeons and GPs are informed on evidence-based recommendations concerning aftercare as described in several guidelines [2, 7].

Patients randomly assigned to GP-led follow-up and aftercare will be referred to their GP for postoperative follow-up and aftercare according to the national guideline (Tables 1 and 2). An information letter provided by the treating surgeon will be given to the GP. This letter contains information about surgery, any complications, disease stage, the use of chemotherapy, subsequent side effects, and risk of recurrence of the referred patient. If the treating surgeon or oncologist recommends an altered follow-up schedule, they will give clear advice.

**Table 1 Tab1:** Follow-up after colon carcinoma resection with curative intent of carcinoma limited to submucosal involvement (T1N0M0)

	Year 1	Years 2-5
Office visits	Every 6 months	Yearly
Physical examination	Only if indicated	
Coloscopy of computed tomography colonography	Within 3 months postoperatively if preoperatively the colon was not visualized completely.	3 years after the last coloscopy, followed by coloscopies each 3–5 years depending on the number, size, and localization of polyps
	If whole colon is visualized preoperatively, coloscopy after 1 year.	

The table is not applicable after endoscopic polypectomy of a T1 carcinoma

**Table 2 Tab2:** Follow-up after colon carcinoma resection with curative intent of carcinoma extending beyond the submucosa but without distant metastasis (all stages with the exception of T1N0)

	Year 1	Year 2	Year 3	Years 4-5
Office visits	Every 6 months	Every 6 months	Every 6 months	Yearly
Physical examination	Only if indicated			
Carcinoembryonic antigen monitoring	Every 3 months	Every 3 months	Every 3 months	Every 6 months
Abdominal ultrasonography (or CT abdomen^a^)	Every 6 months	Every 6 months	Yearly	Yearly
Coloscopy of CT colography	Within 3 months postoperatively if preoperatively the colon was not visualized completely.		3 years after the last coloscopy, followed by coloscopies each 3–5 years depending on the number, size, and localization of polyps	
	If whole colon is visualized preoperatively, coloscopy after 1 year			

^a^Computed tomography (CT) scan is indicated if an abdominal ultrasonography is not readily interpretable (e.g., in the presence of liver steatosis), or a CT scan can be considered in patients with a high risk of recurrence (T4N+) because of its higher sensitivity

#### Intervention 2 (the use of the Oncokompas^2.0^)

Patients who are allocated to the eHealth application Oncokompas^2.0^ (http://www.oncokompas.nl/) will receive an account to be able to make use of the online application. Patients who do not have the availability of internet at home or do not possess sufficient eHealth literacy skills will be supported in the use of Oncokompas^2.0^ by a trial nurse. Oncokompas^2.0^ is an online self-management application which facilitates access to supportive care in cancer survivors. Oncokompas^2.0^ consists of three components: (1) Measure, (2) Learn, and (3) Act [10].

In the “Measure” component, cancer survivors can independently complete PROs targeting the following quality-of-life domains: physical functioning, psychological functioning, social functioning, healthy lifestyle, and existential issues. Data from the “Measure” component are processed in real time and linked to tailored feedback to the cancer survivor in the “Learn” component. In the “Learn” component, feedback is provided to the participant on the level of the topics (e.g., depression and fatigue) by means of a three-color system: green (no elevated well-being risks), orange (elevated well-being risks), and red (seriously elevated well-being risks). Cancer survivors receive elaborated personalised information on the outcomes; for example, on the topic of depression, information is provided on the symptoms of depression and the proportion of cancer survivors who have depression. Special attention is paid to evidence-based associations between outcomes. For example, additional feedback on the association between depression and fatigue is provided if a participant has an orange or a red score on depression as well as on fatigue. The feedback in the “Learn” component concludes with comprehensive self-care advice (tips and tools). All this advice is tailored to the individual cancer survivor.

In the “Act” component, survivors are provided with personalised supportive care options on the basis of their PRO scores and expressed preferences (e.g., guided or unguided interventions and preference for individual therapy versus group therapy). If a participant has elevated well-being risks (orange score), the feedback includes suggestions for self-management options. If a participant has “seriously elevated well-being risks” (red score), the feedback includes advice to contact their own medical specialist or GP for further medical evaluation. Supportive care options are extracted from a national database with those options.

Oncokompas^2.0^ comprises a generic module for all cancer survivors, targeting psychological functioning (anxiety, depression, fear of recurrence, and cognitive functioning), physical functioning (pain, sexuality, sleep, fatigue, body image, diarrhoea, constipation, hearing, loss of appetite, nausea/vomiting, lymph oedema, dyspnoea, and functioning in daily living), social functioning (social life/loneliness, relationships, financial issues, return to work, and communication with care providers), healthy lifestyle (smoking, alcohol use, exercising, nutrition, weight, and stress), and life questions. Furthermore, a tumour-specific module for colon cancer, targeting bladder and urinary problems, heredity, stools, ostomy, pain, and abdominal bloating, is available for study participants of the I CARE study.

### Outline of the study and data collection procedures

Approximately 3–4 weeks postoperatively, patients will be seen at the surgical outpatient clinic. At this visit, a clinical examination will be performed, and information about the histology and results of the surgery will be shared with each patient. Patients not receiving adjuvant chemotherapy and eligible for study inclusion will be asked for their informed consent. Also, patients who need adjuvant chemotherapy and are eligible for study inclusion will be asked for their informed consent. However, before final inclusion in the study, the patients will be referred to the oncologist for chemotherapeutic treatment. After completion of adjuvant chemotherapy, these patients will be included definitively.

After a patient has given informed consent, the GP is contacted if he or she wants to participate in the study. If the GP participates, the patient is finally randomised.

If a patient declines randomisation (or the GP of the patient declines randomisation), the patient is asked to participate in a patients’ preference group and will receive surgeon-led follow-up and aftercare. Patients allocated to GP-led follow-up may be referred back to the hospital at any time during the study. Similarly, patients in the surgeon-led groups are free to consult their GP any time during the study. Subjects can leave the study at any time for any reason without any consequence.

#### Outcomes

Data will be collected in all groups in identical ways and at identical time points. Changes in health status and valuation over time will be measured by using the following questionnaires:Generic and disease-specific quality-of-life questionnaires (EORTC QLQ-C30, EORTC QLQ-CR29, and EQ-5D-5 L) [25–27].Patients’ satisfaction (consumer quality index questionnaire) is measured [28].A short list of questions concerning smoking habits, height, weight, physical exercise, and perceived autonomy (based partly on existing questionnaires) [29, 30].Patient activation (Patient Activation Measure questionnaire) and perceived efficacy in patient-physician interactions (5-item Perceived Efficacy in Patient-Physician Interaction Questionnaire (PEPPI-5) questionnaire) [31, 32].Short questionnaire on process evaluation regarding Oncokompas^2.0^.

The majority of these questionnaires will be filled out directly after the first postoperative visit at the outpatient clinic department and after 3, 6, 12, 24, 36, 48, and 60 months. Extractions from the GPs’ electronic medical record (EMR) and PROs will be used to evaluate preventive care. We will use the EQ-5D-5 L to calculate quality-adjusted life years. For the economic evaluation, health-care utilisation will be measured by using the iMTA Medical Consumption Questionnaire (iMTA MCQ) [33]. The Short-Form Health and Labour Questionnaire (SF-HLQ) will be used to measure absenteeism from paid and unpaid work.

GPs will be asked at the end of the study to fill out a short questionnaire to evaluate care. Focus group interviews are planned with patients and health-care professionals (GPs, surgeons, and nurses involved in aftercare) to evaluate their experiences, limitations, and recommendations.

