**Methods/Design:**

This is a multi-centre 2 × 2 factorial randomised controlled trial with a calculated sample size of 300 patients. Patients with stage I, II, or III colon carcinoma are eligible. Patients will be randomly assigned in four groups: (1) usual follow-up visits and aftercare provided in secondary care, (2) usual follow-up visits and aftercare provided in secondary care with additional use of Oncokompas^2.0^, (3) follow-up and aftercare in primary care, and (4) follow-up and aftercare in primary care with additional use of Oncokompas^2.0^. The primary outcome is quality of life. Secondary outcomes include physical outcomes, psychosocial outcomes, number of investigations, referrals and related communication between secondary and primary care, (time of) recurrence detection and protocol adherence, attention to preventive care, self-management of patients, patient satisfaction, and preference of care at the end of the trial. Data collection will be done by questionnaires and extractions from electronic medical records.

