Therefore, the aims of this study are to determine the efficacy of GP-led follow-up and aftercare compared with secondary care-led follow-up and aftercare among patients with colon cancer and to determine the added value of the eHealth self-management application Oncokompas^2.0^. We hypothesize that GP involvement improves aftercare and preventive care, resulting in improved quality of life and patients’ satisfaction. Furthermore, we hypothesize that a GP-led recurrence detection programme (follow-up) for patients after curative treatment of colon cancer leads to at least equal detection of recurrences and subsequently an equal number of curative recurrence resections. Finally, we hypothesize that usage of Oncokompas^2.0^ facilitates patients’ self-management and personalised access to supportive care in cancer.

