#### Analysis of main study parameters

All analysis will be performed according to the intention-to-treat principle. Crude data are presented with statistical comparison made between randomisation groups on the basis of chi-squared tests for binary or categorical data, the *t* test or analysis of variance as appropriate for comparing group means, and the Kruskal-Wallis test for comparing medians. For continuous normally distributed data, the analysis-of-variance test will be used. The primary analysis will be the comparison between factors, and the comparison between study arms will be part of a secondary, exploratory analysis. For these purposes, univariate and multiple linear or logistic regression analyses will be performed. Quality of life will be assessed through multi-level modelling. A two-sided *P* value of less than 0.05 will be considered statistically significant. Nevertheless, in all appropriate cases, 95 % confidence intervals will be given. Changes in health status and valuation over time will be measured by using the questionnaires mentioned above. Next to validated questionnaires and prospective monitoring of the trial endpoints, extractions from the GPs’ EMR and patients’ hospital records will be used to complete the data.

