Costs will be discounted at 4 % and effects at 1.5 % as recommended by the Dutch guidelines for costing studies [29]. Missing cost and effect data will be imputed by using multiple imputation according to the MICE (Multiple Imputation by Chained Equations) algorithm developed by Van Buuren et al. [37]. Costs typically have a highly skewed distribution [38]. Therefore, bias-corrected and accelerated bootstrapping with 5000 replications will be used to estimate 95 % confidence intervals around the mean difference in total societal costs between the groups. Incremental cost-effectiveness ratios (ICERs) will be calculated by dividing the difference in mean total costs between the groups by the difference in mean effects between the groups. Bootstrapping will be used to estimate the uncertainty surrounding the ICERs which will be graphically presented on cost-effectiveness planes. Cost-effectiveness acceptability curves will also be estimated. Cost-effectiveness acceptability curves show the probability that care by GPs is cost-effective in comparison with usual care for a range of different ceiling ratios, thereby showing decision uncertainty [39]. The iMTA MCQ and SF-HLQ questionnaires will be sent to the participant simultaneously with the quality-of-life questionnaires (EQ-5D-5 L) to facilitate patient’s response. Besides the information provided by the patients themselves by means of the methods mentioned above, the researchers will systematically gather data directly from hospital and GP files. This information will be used to compare health-care usage and be correlated to compare health-care costs. The following items will be checked at the time intervals mentioned above: outpatient clinic visits, GP practice visits, telephone consultations, hospital admittances (number of days), laboratory tests, all medical imaging, endoscopies, referrals to (other) medical specialist care, referrals to paramedical care, and drug prescriptions. Note that health-care use in both primary and secondary care will be evaluated for patients allocated to any group of randomisation to create a complete survey of health-care use.

Each single item will be stored in the case record file created for each participant. Via this information from health-care use, the costs used by each participant will be determined by using standardised reference lists.

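### The sources named for preventive care leave out the hospital record; if that wording governs, the GP-led versus surgeon-led comparison of this secondary outcome could be biased towards GP-led care

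*Protocol article*

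**What the plan says.** The abstract of the protocol article (Methods/Design) lists among the secondary outcomes "attention to preventive care, self-management of patients, patient satisfaction, and preference of care at the end of the trial". The last paragraph of the Background attaches a direction to it: "We hypothesize that GP involvement improves aftercare and preventive care".

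One sentence, in the Outcomes section, assigns data sources to this outcome. It names extractions from the GPs' "electronic medical record (EMR) and PROs will be used to evaluate preventive care". The hospital record is not mentioned there. The same section states that "Data will be collected in all groups in identical ways and at identical time points", and its questionnaire list includes "A short list of questions concerning smoking habits, height, weight, physical exercise, and perceived autonomy".

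Two other places mention hospital files. Analysis of main study parameters says that, next to questionnaires and prospective monitoring of the endpoints, extractions from the GPs' EMR and "patients’ hospital records will be used to complete the data". The Economic evaluation analysis says that "the researchers will systematically gather data directly from hospital and GP files". Neither place names preventive care.

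**The concern.** Randomisation on the first factor decides who provides follow-up and aftercare, and so also in which record that provider writes. A GP who gives lifestyle advice at a follow-up visit notes it in the GP record. A surgeon or hospital nurse who gives the same advice would ordinarily note it in the hospital record. Using one source in every arm is identical collection, but it does not give equal capture when one arm's provider writes elsewhere.

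At stake is the comparison that bears on the hypothesis about preventive care. Incomplete capture in the surgeon-led groups would lower their apparent rate and so favour GP-led care, which is the direction hypothesised. Intention-to-treat analysis and a larger sample do not remove an error of this kind; a larger sample makes it more likely to reach significance.

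**Working it through.** **1. The plan's own figure.** The article gives no number for preventive care. Its sample size is for quality of life: a difference of 10, SD 20, two-sided alpha 0.05, power 80 %. The normal approximation gives 2 × (1.960 + 0.842)² × 20² / 10² = 62.8, so 63 per group. The t-test version gives 63.8, so 64, as stated. This is used only to fix group sizes: each level of the GP factor pools two of the four groups, so 2 × 64 = 128 analysable patients per side (2 × 75 = 150 before drop-out).

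**2. The sources side by side.**
- Outcomes section: GP record and PROs, stated for preventive care by name.
- Analysis of main study parameters: GP record and hospital record, stated for the data in general.
- Economic evaluation analysis: hospital and GP files, for a list of visits, telephone consultations, admissions, laboratory tests, imaging, endoscopies, referrals and prescriptions. Counselling is on the list for neither type of file. Since the Outcomes section nevertheless uses the GP record for preventive care, this costing list cannot show what is extracted for that outcome.
- Listed lifestyle questions: smoking, height, weight and exercise. These describe what the patient does or is, not whether a professional raised the subject.

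The first two entries do not agree on whether hospital records are a source for preventive care.

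**3. Illustration of size.** The following are assumptions, not figures from the documents:
- p = true proportion receiving preventive care, equal in both arms, 0.30 or 0.50;
- h = share of that care in the surgeon-led arm noted only in hospital, 0.10, 0.25 or 0.50;
- r = share of the missed care recovered through PROs or hospital files, 0, 0.5 or 1;
- complete capture in the GP-led arm, and a binary outcome.

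Observed surgeon-led proportion: q = p × [1 − h(1 − r)]. False difference: d = p − q = p × h × (1 − r). With n = 128 per side, SE = √{[p(1 − p) + q(1 − q)] / n}, and the probability of a significant result is Φ(d/SE − 1.96) + Φ(−d/SE − 1.96).

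Worked case, p = 0.50, h = 0.25, r = 0: q = 0.375, d = 0.125, SE = √[(0.2500 + 0.2344) / 128] = 0.0615, d/SE = 2.03, probability 52.9 %.

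| p | h | d, r = 0 | significant, r = 0 | d, r = 0.5 | significant, r = 0.5 |
|---|---|---|---|---|---|
| 0.30 | 0.10 | 3.0 points | 8.3 % | 1.5 points | 5.8 % |
| 0.30 | 0.25 | 7.5 points | 27.8 % | 3.75 points | 10.2 % |
| 0.30 | 0.50 | 15.0 points | 83.2 % | 7.5 points | 27.8 % |
| 0.50 | 0.10 | 5.0 points | 12.6 % | 2.5 points | 6.8 % |
| 0.50 | 0.25 | 12.5 points | 52.9 % | 6.25 points | 17.1 % |
| 0.50 | 0.50 | 25.0 points | 99.0 % | 12.5 points | 52.9 % |

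With r = 1, d = 0 and the rejection rate is the nominal 5 %. At 150 per side the differences are the same and the probabilities slightly higher.

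**The case against.** The strongest reply is that hospital records are already covered. The sentence in Analysis of main study parameters speaks of completing the data without exception, preventive care is a listed outcome, and the Outcomes section does not say that its two sources are the only ones. The article is also a condensed account, and the item-by-item extraction form would sit in the full protocol. This stands in part: one cannot conclude that hospital records are excluded. It does not remove the point, because the article does not simply leave the source unstated. It names sources for this outcome, and the set differs from the general statement.

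A reader might infer that hospital-based preventive care is not counted and that the comparison is therefore biased. The documents do not support that. Hospital files are mentioned twice. Referrals and prescriptions gathered from both settings could show some preventive actions. PROs are collected alike in all arms. The Outline of the study lets surgeon-led patients consult their GP at any time, so the GP record carries information in those groups too.

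A reader might also take the upper figures in the table as the expected error. They require that half of the care be noted only in hospital and that nothing be recovered by any other source. At a 10 % hospital-only share the false-positive rate is about 8–13 %, and it falls further with partial recovery.

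**Conclusion.** The point holds in conditional form. The Outcomes section and the analysis section do not agree on the sources for preventive care. If the Outcomes wording governs, advice recorded only in hospital can be missed in the surgeon-led groups. The listed questionnaire items do not clearly make up for this, and the error would run towards the stated hypothesis.

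The documents do not allow the size to be determined. Under the assumptions shown, the result ranges from no bias (full recovery) to a false difference of 25 points (no recovery, half the care noted only in hospital). The lowest figure without any recovery is 3 points, with about 8 % false significance. The matter concerns one secondary outcome and leaves the primary quality-of-life comparison and its sample size untouched. It is worth correcting because the remedy is cheap and a possible bias in the hypothesised direction would be hard to argue away afterwards.

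**What to change.** Make the Outcomes section and Analysis of main study parameters agree. State that the same list of preventive-care items (for example, advice or referral on smoking, alcohol, exercise, weight and nutrition) is extracted from both the hospital record and the GP record of every randomised patient, in all four groups, and that an item counts if found in either record.

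If hospital extraction of these items is not feasible, base the GP-led versus surgeon-led test on patient-reported items collected identically in all arms, and present the GP-record data descriptively. Because the listed questions concern behaviour, this alternative would compare behaviour rather than attention given by the provider, and the report should say so.

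The cost is a revised sentence and a few more items on the extraction form. The economic evaluation already has the researchers gathering data from hospital and GP files for every randomised group.
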